### Intervention

FAME is offered to families living in family locations and asylum centres. FAME encompasses seven sessions. Apart from the introduction session and final evaluation session, each session has a similar structure. The sessions start with an energizing activity to warm up the participants and promote positive group interactions. Subsequently, the main activity, representing the central theme of the session, takes place. The themes and activities of FAME are based on the metaphor ‘the bucket and the treasure chest’. The bucket is a metaphor for the number of stressful factors and problems families are exposed to. The bucket is filled with soluble and insoluble problems. The treasure chest represents the sources of support the families have. During the programme, families and trainers will focus on questions such as: ‘What are sources of stress in the bucket, and what are sources of support in the treasure chest?’ The bucket and treasure chest can be found in the manual of FAME [6]. The role of the trainer can be described as an ‘eagle’, as he or she walks around the room and zooms in on important positive or problematic interactions that arise. The family members function as ‘consultants’ for each other, as they can offer and receive feedback and support. The sessions are ended by reflecting on what the families have discussed and learned. A manual on FAME for families with children aged six to twelve has been published in Dutch [6]. The programme was further adapted to fit the other age groups addressed in this study. Trainers who offer FAME are therapists working at Centrum ‘45, who have ample experience in working with refugees and asylum-seekers and in working with FAME. Table 2 lists the sessions, themes, and aims of FAME.

**Table 2 Tab2:** Sessions of FAME

Session	Theme	Aims
1. Introduction	Introduction of FAME, participants, and therapists	Parents know the aim of FAME. Mutual expectations are identified. Methods and framework of FAME are explicated. Parents are introduced to the study. Parents and children feel motivated to take part in the group.
2. Bucket and treasure chest	Stressors and sources of support	Parents are aware of the impact of difficulties on thoughts, behaviour, emotions and relationships. Parents recognize difficulties and risk factors. Parents can distinguish between soluble and insoluble problems. Parents experience mutual recognition. Parents start to develop the following insight: you can do something to decrease stress (locus of control). Families have a positive experience.
3. Impact	Parent-child relationship and the impact of difficulties	Parents are more aware of their own stress reactions. Parents can differentiate between different stress reactions (e.g. rumination, sadness, sleeping problems). Parents are aware of the impact of their stress on the parent-child relationship. Parents realize how they can aid their children. Parents develop an understanding of what they and their children need to facilitate positive development.
4. Tools	Resources and coping; development of the child	Parents gain insight in how to deal with difficulties, and how they are already dealing with difficulties. Parents increase and improve their coping strategies, learn from each other. Parents experience positive interactions with each other. Parents know what helps them to control their own emotions.
5. Discovering	Resources and coping; strengths within the family	Parents become aware of the impact of their own emotions on their child. Parents become aware of how their children perceive the world and emotions of their child.
6. Treasure map	Social support	Parents obtain insight in how they can ask for help. Parents obtain insight in how they can offer help. Parents become more aware of their self-worth.
7. Closing session	Concluding FAME; leave-taking	Looking back: What did you learn? Looking forward: How will you use the things you learned during FAME in the future? Self-confidence of participants is stimulated. Participants develop ideas on how to hold onto and use acquired insights.

Overview of themes and aims for all age groups

### Procedure

Families in both living conditions follow the same procedure. In cooperation with health teams at family facilities and asylum centres throughout the Netherlands, asylum-seeker families will be invited to take part in an introduction session. Participants will be informed about this initial introduction session through flyers and verbal information offered by local partners and researchers. The aim of the introduction session is to explain certain aspects of the programme, such as the structure, number, and duration of the sessions, and to clarify expectations. Families are given the opportunity to ask any questions they might have. During the week after the introduction session, families that have stated their interest in taking part in the programme will be visited. During this visit, any further questions can be answered. Participants who want to take part in the study are then asked to fill in a written informed consent. Parents fill in an informed consent for their children under the age of 16. Minors over 12 years of age fill in an informed consent as well.

Families who agree to take part in the study are subjected to pre-test measures (*t*_1_). One of the researchers will either visit them at home or arrange a quiet room. A professional (telephone) interpreter will be provided. During this visit, parents will be asked to fill out questionnaires (see the ‘Measurements’ section), and a semi-structured interview with the parents will take place. If the participants agree, their semi-structured interviews will be audio-recorded. If the family members agree to take part in videotaping, the parent-child relationship will subsequently be assessed by videotaping the interaction between parent and child for approximately 20 min. Pre-test measures will last approximately 90 min for the parents, and 20 min for the children.

As noted, FAME involves seven weekly 2–3-h sessions. One or two official interpreters will be provided in each group. At the end of each session, the participants are asked to fill in scales measuring their distress and how they rate the session (*t*_2_). The scales will be explained by the trainer, who is aided by the interpreters. Moreover, during the sessions, a researcher will evaluate programme integrity using a predetermined programme integrity list (see below). The final assessment (*t*_3_) takes place in the week after the last session of FAME. The participants will be visited at home or a private room will be arranged. A (telephone) interpreter will be provided. The parents and children aged five and over will take part in individual semi-structured interviews. Parents will fill in questionnaires. Post-test measures will last approximately 65 min for the parents and 30 min for the children. See Table 3 for the schedule of enrolment, intervention, and assessment.

**Table 3 Tab3:** Schedule of enrolment, intervention, and assessment

		Parents			Children		
Time point	Enrolment	*t* _1_	*t* _2_	*t* _3_	*t* _1_	*t* _2_	*t* _3_
Enrolment							
Eligibility screen	X						
Informed consent	X						
Information session	X						
Assessments							
SCORE-15		X		X			
PHQ-4		X		X			
Semi-structured interview		X		X			X
Demographics		X					
EAS		X			X		
((Y)C)ORS			X			X	
((Y)C)SRS			X			X	
Programme integrity list			X			X	

*t*_1_, pre-FAME; *t*_2_, weekly assessments during FAME; *t*_3_, post-FAME. *EAS* Emotional Availability Scales, *PHQ-4* Patient Health Questionnaire for Depression and Anxiety, *SCORE-15* Systematic Clinical Outcome and Routine Evaluation, *((Y)C)ORS* ((Young) Child) Outcome Rating Scale, *((Y)C)SRS* ((Young) Child) Session Rating Scale

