##### Parents and children

Parents and children are subjected to an observational measurement. Quality of the parent-child relationship will be measured using the Emotional Availability Scales (EAS) developed by Biringen et al. [25]. They described emotional availability as ‘the capacity of a dyad to share an emotionally healthy relationship’ (p. 114; [26]). When conducting the EAS, a parent-child dyad is asked to interact as they would usually do for approximately 20 min. These interactions are videotaped and consequently scored on the EAS by certified objective observers with ample experience in working with refugees. EAS measures four caregiver components: sensitivity, structuring, non-intrusiveness, and non-hostility. The child components measured by the EAS are the child’s responsiveness to the caregiver and the child’s involvement with the caregiver. A score on a Likert scale of 1–7 on each component is used for data analysis. A score of 7 suggests that the participant displays optimal behaviours on that scale, a score of 4 indicates inconsistent behaviour, and a score of 1 indicates that the participant displays non-optimal behaviour. Studies suggest that the EAS is universally applicable, and cross-cultural validity has been established in various countries [26, 27].

To monitor participants’ feedback on progress, a self-report scale will be used: the (Young Child) Outcome Rating Scale ((YC)ORS). The (YC)ORS has four single-item subscales: individual, relational, social, and general. Sample questions of the CORS include ‘How am I doing?’ and ‘How are things in my family?’. To assess therapeutic alliance, the (Young Child) Sessions Rating Scale ((YC)SRS) will be used. The four single-item subscales of the (YC)SRS include relationship, goals and topics, approach and method, and overall. Both the (YC)ORS and the (YC)SRS are visual and analogue. Both scales have demonstrated adequate validity, solid reliability, and high feasibility [28, 29].

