### Statistical analysis

#### Analysis of quantitative data

Quantitative data-analysis will be conducted using SPSS 23 (IBM Statistics). Descriptive statistics of demographic data, the programme integrity list, and the rating scales will be presented for all participants. For continuous variables, means, standard deviations, medians, and ranges will be reported. For categorical variables, numbers and percentages will be reported.

To test the hypothesis that families living at family facilities have more problems concerning the parent-child relationship and family functioning and higher parental symptoms of anxiety and depression than families living at asylum centres, pre-test scores on the EAS, PHQ-4, and SCORE-15 will be compared between these two groups using independent *t* tests.

To evaluate whether undergoing FAME coincides with a reduction in parental symptoms of anxiety and depression and improvement in family functioning, differences between the pre- and post-test scores on the SCORE-15 and PHQ-4 will be calculated. If more than 40 participants have completed the pre- and post-test measures, a mixed-design ANOVA will be executed. However, if there is a large amount of missing data, or if less than 40 participants have completed pre-test and post-test measures, two independent *t* tests will be executed. In addition to statistical significance, it is important to report any meaningful clinical change when studying the impact of an intervention. Calculating the Reliable Change Index (RCI), as proposed by Jacobson and Truax [31], allows us to do so. Using the RCI, we will calculate whether the differences in the scores between *t*_1_ and *t*_3_ are greater than the measurement error. A calculated RCI larger than |1.96| indicates a clinically reliable change with 95% certainty. The RCIs allows us to determine the numbers of participants improved, unchanged, and worsened from *t*_1_ to *t*_3_.

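### The Outcome Rating Scale, meant to monitor progress, is completed only after sessions, so it has no pre-programme value and no score can be separated from the session just held

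*Protocol article*

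**What the plan says.** The Procedure section of the protocol article gives both weekly self-report scales at one moment: "At the end of each session, the participants are asked to fill in scales measuring their distress and how they rate the session". Table 3 marks the ORS at *t*2 only, for parents and for children, and its footnote defines *t*2 as "weekly assessments during FAME". The ORS cells at *t*1 (pre-FAME) and *t*3 (post-FAME) are empty.

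Under Measurements, Parents and children, the two scales have different purposes. The ORS has this one: "To monitor participants’ feedback on progress, a self-report scale will be used". On its content: "The (YC)ORS has four single-item subscales: individual, relational, social, and general". The Session Rating Scale (SRS) is there to assess therapeutic alliance.

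The Intervention section gives the sessions a common format of warm-up, main activity and closing reflection ("The sessions are ended by reflecting on what the families have discussed and learned"), but exempts the introduction session and the final session from it.

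Under Analysis of quantitative data, the ORS has a descriptive role: "Descriptive statistics of demographic data, the programme integrity list, and the rating scales will be presented for all participants". The change question is answered elsewhere: "differences between the pre- and post-test scores on the SCORE-15 and PHQ-4 will be calculated".

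**The concern.** End-of-session timing suits the SRS, because that scale rates the session. It suits the ORS less well. A scale for progress over weeks should show the state in which a family arrives, and should have a value from before the programme began. As scheduled, the first ORS score already follows a session of two to three hours, and so does every later one.

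At stake is how a plotted or tabulated ORS course can be read. Readers of a pilot report are likely to take a rising course as progress since the start of FAME, and the schedule does not supply the value that this reading needs. The section on integrating quantitative and qualitative data also asks, family by family, whether the two sources agree. For children, the ORS is the only repeated measure of functioning that enters that comparison.

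**Working it through.** No sample size, power or error rate is involved. The check is a count from the schedule, followed by a short argument about what the scores contain.

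**1. Count of ORS occasions.** There are seven weekly sessions (Procedure; Table 2), with the ORS at the end of each and nowhere else.

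- Before FAME: 0
- Directly after a session: 7
- At the post-test visit: 0

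So each participant has at most 7 values, all post-session. This takes session 1 of Table 2 to be separate from the recruitment meeting, which Procedure calls an introduction session and Table 3 lists under enrolment as an information session. If the two were the same meeting, it would come before consent. At most 7 − 1 = 6 values would remain, still all post-session.

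**2. What a first-to-last change contains.** Write *S*ₖ for a participant's underlying state at session *k*, *S*₀ for the state before FAME, and *L*ₖ for any immediate effect of session *k*. The observed score is *S*ₖ + *L*ₖ. Then:

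- Observed change, session 1 to session 7 = (*S*₇ − *S*₁) + (*L*₇ − *L*₁).
- The change *S*₁ − *S*₀ is not observed.

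If the immediate effect is the same after every session, *L*₇ − *L*₁ = 0: the level shifts, but the trend is preserved. If it differs between sessions, the difference enters the change. The documents give neither the size nor the sign of *L*ₖ, so no figure can be put on it. They do give a reason not to assume equality at the two ends: sessions 1 and 7 are the two that the Intervention section exempts from the common format. In Table 2, session 1 introduces aims, expectations and framework, while session 7 looks back, takes leave and aims to raise self-confidence. The 7 − 2 = 5 sessions in between share one format.

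**3. What else children have over time** (Table 3):

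| Measure | Children |
|---|---|
| SCORE-15, PHQ-4 | none |
| EAS | *t*1 only |
| Interview | *t*3 only |
| ORS | weekly *t*2 |
| SRS | weekly *t*2, rates the session |
| Programme integrity list | weekly *t*2, completed by a researcher, about the session |

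The ORS is therefore not the only repeated measure in children, but it is the only repeated measure of their functioning.

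**4. Effect of moving the ORS to the start of the session.** There are again 7 occasions: 1 before any programme activity (start of session 1) and 6 at the start of later sessions, each about a week after the previous session.

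**The case against.** The strongest reply is that nothing inferential depends on the ORS. The objective on change concerns parental symptoms and family functioning. It is answered with the SCORE-15 and PHQ-4, both taken at *t*1 and *t*3 outside the sessions, with the Reliable Change Index added. The rating scales are only described, no objective names quantitative change in children, and the Discussion already says that effects cannot be attributed to FAME. All of this stands, and it limits the weight of the point. It does not remove it: a described course is still read, and the stated purpose of the scale is progress.

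Second, session 1 is introductory; work on stressors begins in session 2. A score after session 1 precedes most of the active content, so it is an imperfect baseline rather than a worthless one. That also stands. A reader might infer that all early change is lost. The documents support only that change up to and during session 1 is not captured.

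Third, some tempting stronger readings go beyond the text:

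- That the ORS records post-session mood. The items are wider than mood and no recall period is stated. What can be said is that a score cannot be separated from any immediate effect of the session.
- That the series must follow the session themes. This is possible but not shown. Session 2, on stressors and support, also aims at a positive experience, and session 5 deals with the effect of parents' emotions on the child.
- That the ORS course says nothing about progress. A constant immediate effect would leave the trend intact.

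Finally, recruitment began in September 2018 with an approximate duration of 12 months, so a change partway would mix two timings. This is a fair objection to pooling, and the fix deals with it.

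**Conclusion.** The point holds in a limited form. The ORS has no pre-programme value for any participant, every score directly follows a session, and the longest available change runs between the two sessions that differ in format from the rest. Nothing elsewhere in the article repairs this.

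The size is a count: 0 of at most 7 values precede FAME. The planned totals are about 90 parents and 90 children, but these are upper bounds for the number affected. The age range starts at 0, infants cannot complete a self-report scale, and the Discussion expects dropout. The size of any immediate session effect is unknown.

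A reader might infer that the parental pre-post results are compromised. They are not, because they use other measures taken at separate visits. The consequence lies in the reading of the descriptive ORS course, chiefly for children. This is a worthwhile low-cost improvement rather than a fault in the main analysis. The conclusion assumes that the Procedure text and Table 3 give the complete ORS schedule.

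**What to change.** In the Procedure section, give the ((Y)C)ORS at the start of each session, before the energizing activity or any other content, and keep the ((Y)C)SRS at the end. Name the start-of-session-1 score as the pre-programme value, and describe change from it to the start of session 7. State in Table 3 that the two scales fall at different moments of the session.

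The alternative is to add the four-item ORS at the *t*1 visit, where an interpreter is already provided. This supplies a pre-programme value, but the later scores would still be post-session, so change from *t*1 would mix progress with any immediate session effect and should be labelled accordingly.

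The first option adds no items and no staff. The trainer's explanation of the ORS through the interpreters moves to the start, so the scales are handled in two moments instead of one. Families who arrive late may miss that week's ORS, and the start-of-session-7 score does not reflect session 7. The second option adds four items to the pre-test visit.

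For groups already run under the current timing, report the ORS as a within-programme, post-session series and not as change from baseline, and do not pool it with start-of-session scores.

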### Measurements

#### Quantitative

##### Parents

Family functioning will be measured using the Systemic Clinical Outcome and Routine Evaluation (SCORE-15; [20]). The SCORE-15 is a 19-item self-report questionnaire that can be used to monitor and report indicators of progress in systemic therapy. It offers an overall measure of family functioning as well as sub-scale scores on the dimensions: strength and adaptability, overwhelmed by difficulties, and disrupted communication. The validity of the SCORE-15 as an index of therapeutic change has been established. The questionnaire demonstrates good test-retest reliability, construct validity, and responsiveness in terms of clinical and reliable change [21, 22].

Parental symptoms of depression and anxiety will be assessed using the 4-item Patient Health Questionnaire for Depression and Anxiety (PHQ-4; [23]). The PHQ-4 has been validated in the general population. The total score is an index of anxiety and depression severity [24].

The following demographics of the participating family members will be collected: age, gender, country of origin, time spent in the Netherlands, number and age of family members, and educational level.

##### Parents and children

Parents and children are subjected to an observational measurement. Quality of the parent-child relationship will be measured using the Emotional Availability Scales (EAS) developed by Biringen et al. [25]. They described emotional availability as ‘the capacity of a dyad to share an emotionally healthy relationship’ (p. 114; [26]). When conducting the EAS, a parent-child dyad is asked to interact as they would usually do for approximately 20 min. These interactions are videotaped and consequently scored on the EAS by certified objective observers with ample experience in working with refugees. EAS measures four caregiver components: sensitivity, structuring, non-intrusiveness, and non-hostility. The child components measured by the EAS are the child’s responsiveness to the caregiver and the child’s involvement with the caregiver. A score on a Likert scale of 1–7 on each component is used for data analysis. A score of 7 suggests that the participant displays optimal behaviours on that scale, a score of 4 indicates inconsistent behaviour, and a score of 1 indicates that the participant displays non-optimal behaviour. Studies suggest that the EAS is universally applicable, and cross-cultural validity has been established in various countries [26, 27].

To monitor participants’ feedback on progress, a self-report scale will be used: the (Young Child) Outcome Rating Scale ((YC)ORS). The (YC)ORS has four single-item subscales: individual, relational, social, and general. Sample questions of the CORS include ‘How am I doing?’ and ‘How are things in my family?’. To assess therapeutic alliance, the (Young Child) Sessions Rating Scale ((YC)SRS) will be used. The four single-item subscales of the (YC)SRS include relationship, goals and topics, approach and method, and overall. Both the (YC)ORS and the (YC)SRS are visual and analogue. Both scales have demonstrated adequate validity, solid reliability, and high feasibility [28, 29].

##### Programme integrity

To evaluate whether the programme is feasible and can be executed as intended, we developed a programme integrity list. This checklist is based on the four dimensions of programme integrity [30]: (1) *Adherence*, the specified components of the programme; (2) *Exposure*, the extent to which family members are exposed to the programme, by monitoring presence and duration (presence is measured by registering the number of minutes each family is present and duration by monitoring the duration of each session in minutes); (3) *Quality of delivery*, therapeutic skills and competence, measured by scoring items such as ‘zoomed in on problematic interactions’ and ‘allowed participants to practise with learned behaviours’; (4) *Participant responsiveness*, measured by assessing reactions during the session, including positive interactions (e.g. laughter) and active participation. Additional questions about participant responsiveness will be asked during the semi-structured interview (*t*_3_). We aim to observe all FAME sessions offered during this study. All assessors will be trained in using the programme integrity list. Two independent assessors will be present during several sessions to fill in the programme integrity list. Inter-rater reliability will be calculated.

